### Study medication accountability

Study drug accountability will be assessed and documented by Guy’s Hospital Pharmacy. Study vials that have been reconstituted in saline for injection and used will be stored separately at room temperature after use for return to pharmacy for drug accountability to be assessed.

### Concomitant medications

Rescue medications will be provided to participants before and throughout the pollen season. These will include: desloratadine (5 mg, up to 1 tablet daily), (olopatadine eye drops, 1.0 mg/mL, up to 1 drop per eye twice daily), fluticasone propionate nasal spray 50 mcg per spray, up to 2 sprays per nostril once daily), and prednisone (for use at 30 mg per day for up to 5 days). Participants will be asked to use only these medications to treat their hay fever symptoms on an as required basis. However, participants who are not getting hay fever symptoms will be encouraged to try not to use these medications. Participants will be asked to use only these medications. A short course of prednisolone will be available if symptoms are particularly severe. Participants will be instructed to contact a trial physician prior to taking any prednisolone. The doctor will then provide instructions on dose and duration of treatment. Concurrent treatment with beta-blockers, calcium channel blockers, tricyclic antidepressants, monoamine oxidase inhibitors or anti-IgE monoclonal antibody will not be permitted.

### Randomisation

The King’s Clinical Trial Unit (KCTU) at King’s College London will host a 24 hour web based randomisation system. Participants will be randomised 1:1 to active and comparator medications by the method of block randomisation with randomly varying block sizes, stratified by the size of skin test response to grass pollen at screening visit (the cut-off skin prick test size will be the median value of all subjects to be randomised) and presence/absence of rhinitis symptoms outside the grass pollen season. Study medication will be blinded. To minimise bias through accidental unblinding as a result of common injection site reactions in the active trial arm, the control intervention will consist of a reducing dose of histamine, which will produce similar clinical effects as the active medication. All physicians, researchers, research nurses, outcome assessors and patients will remain blinded to treatment allocation until the primary analysis is completed. The trial statistician will be sub-group unblind only. The KCTU randomisation service provider and the manufacturing pharmacy only will have access to the blinding information for the study.

In August 2013, KCTU will randomly select participants to be approached in rotation to undergo skin biopsies. The first 40 participants who agree will then undergo biopsy after giving additional procedure-specific informed consent. Also in August 2013, KCTU will randomise all participants for a second time to one of three groups (3 months, 6 months or 12 months). These 3 groups will then undergo repeat intradermal allergen injections at 3, 6 or 12 months, respectively, to assess if low dose intradermal allergen immunotherapy is associated with prolonged suppression skin responses.

### Withdrawal of participants

The study therapy (active or control) will be discontinued for any of the following reasons:

1. Inability or failure to attend for intervention within 3 weeks of previous administration.

2. Inability or failure to receive 7 or 8 injections within the dates specified.

3. Two Grade 2 systemic reactions, or a single systemic reaction of Grade 3 or above after administration of study therapy. Systemic reactions will be graded according to the World Allergy Organization (WAO) criteria:

•Grade 1: symptoms of 1 organ system (cutaneous, upper respiratory tract, conjunctival, gastrointestinal, other);

•Grade 2: symptoms of more than 1 organ system present or asthma symptoms/signs (cough, wheezing, shortness of breath but < 40% drop in peak expiratory flow [PEF] or FEV1).

•Grade 3: asthma symptoms/signs (with ≥ 40% drop in PEF or FEV1), upper respiratory tract (laryngeal, uvula, tongue) oedema with or without stridor.

•Grade 4: respiratory failure or hypotension with or without loss of consciousness.

4. An adverse event that, in the judgment of the principal investigator or the medical monitor, presents an unacceptable consequence or risk to the participant.

5. An illness or infection that is not associated with the condition under study and that requires treatment not consistent with protocol requirements; or, if a participant develops an intercurrent illness that in the judgment of the principal investigator in any way justifies discontinuation.

6. An inability or unwillingness to comply with the study protocol, and the protocol deviations are sufficient to jeopardise the participant’s well-being or the integrity of the study.

7. Pregnancy occurs during study participation.

Participants have the right to withdraw from the study at any time for any reason. The investigator also has the right to withdraw patients from the study drug in the event of inter-current illness, AEs, SAE’s, SUSAR’s, protocol violations, cure, administrative reasons or other reasons. As an excessive rate of withdrawals could render the study uninterpretable unnecessary withdrawal of patients will be avoided where possible. Should a participant decide to withdraw from the study, all efforts will be made to report the reason for withdrawal as thoroughly as possible. Should a participant withdraw from study drug only, efforts will be made to continue to obtain follow-up data, with the permission of the patient. A 10% allowance has been included in the sample size to account for withdrawal and participants will only be replaced if this occurs prior to randomisation. The statistical analysis also incorporates a plan for dealing with missing data from symptom and medication diary cards.

### Assessment of efficacy

#### Primary efficacy parameters

The primary outcome measure will be daily symptoms and medication use during the 2013 grass pollen season. The scoring systems have been adapted from previous trials of grass pollen immunotherapy [29]. Participants will record symptom scores each day (reflecting the preceding 24 hours) in diary cards from mid-May through to the end of August. The symptom score will be based on individual symptoms in the nose (sneezing, blockage, and running), eyes (itching, redness, tears, and swelling), mouth and throat (itching and dryness), and chest (breathlessness, cough, wheezing, and tightness), recorded on a scale of 0 to 3 (with a score of 0 indicating no symptoms and 1, 2, and 3 indicating mild, moderate, and severe symptoms, respectively). The maximum daily symptoms score will therefore be 39. All possible rescue medications will be provided to each participant approximately 2 weeks before and throughout the pollen season. Participants will be asked to use medications to treat symptoms on an as required basis. Daily medication use will also be recorded in diary cards by participants and a medication score calculated based on use according to need of the following medications: desloratadine, 5 mg, up to 1 tablet daily (6 points per day); olopatadine eye drops, 1.0 mg/mL, up to 1 drop per eye twice daily (1.5 points per drop, up to 6 points per day); fluticasone nasal spray, 50 mcg per spray, up to 2 sprays per nostril once daily (2 point per spray, up to 8 points per day); and prednisone, 5 mg per tablet, up to 6 tablets per day (2 points per tablet, up to 12 points per day). All these medications will be provided to participants free of any charge. The maximum daily medication score will therefore be 32. For each participant, both the symptom score and the medication score will be individually expressed as area under curve (AUC) values for the period corresponding to the grass pollen season (mid May - August 2013). Since maximum scores for symptoms and medications are different in magnitude these parameters will be normalised as recommended World Allergy Organization guidelines [30]. Normalised AUC scores will then be added together to generate a combined symptom and medication score in accordance with World Allergy Organization guidance on immunotherapy trials [30]. Efficacy will then be assessed by comparison of this combined score in active and control groups.

#### Secondary efficacy parameters

The following will be compared in active and control groups:

1) Symptom scores (AUC) calculated as above.

2) Medication scores (AUC), calculated as above.

3) Rhinoconjunctivitis Quality of Life: mini Rhinitis Quality of Life Scores (RQLQ) scores (overall score and domain scores) will be recorded three times during the pollen season (June 12, June 26 and July 10) and once after the season on 4 September 2013. These values will be compared in active and control groups. The mini RQLQ covers five dimensions of health including sleep, non-nose/eye symptoms, practical problems, nasal symptoms, eye symptoms.

4) Health related quality of life: This will be evaluated using the EQ-5D-5L questionnaire three times during the pollen season (June 12, June 26 and July 10) and once after the season on 4 September 2013.

5) Visual Analogue Scores (see Additional file 1). These will be recorded every 2 weeks during the pollen season and AUC values calculated.

6) Global evaluation scores (see Additional file 2).

7) The number of primary care (i.e. general practitioner) visits for hay fever during summer 2013.

8) Combined symptom and medication scores during the peak* of the 2013 grass pollen season.

9) Number of medication free days covering the grass pollen season period of 13th May-end August 2013 will be compared in active and control groups.

10) Number of symptom free days covering the grass pollen season period of 13th May-end August 2013 will be compared in active and control groups.

11) Individual symptoms scores (AUC) for each organ: nose, mouth, eyes and lungs.

12) Total number of days during which prednisolone used between 13th May-end August 2013.

*The peak of grass pollen season will be defined as starting on the first 3 consecutive days between 13 May and 31 August 2013 when grass pollen counts in central London are ≥ 30 grains/cm^3^, using counts supplied by the UK Met Office. The end of the peak season will be defined as the first of 3 consecutive days when grass pollen counts are < 30 grains/cm^3^. In the event of 2 or more peaks during the 2013 season, these individual peak periods will be analysed separately.

The persistence of late response suppression will be evaluated by randomising active and control subjects in Aug 2013 into 3 groups. Each group will receive a follow-up intradermal injection of 10 BU (33.3 SQ-U) of grass pollen allergen, as well as a diluent control injection, at either 3, 6 or 12 months. Reversal of late response suppression will be assessed at each time point by comparing mean late response size in the active and control groups.

### Procedures for assessing efficacy parameters

#### Primary efficacy parameters

All participants will be supplied with diary cards. They will be asked to score symptoms and medication use for each day. Participants will be asked to provide a copy of the first diary card (corresponding to 13–30 May 2013) during the first week of June by post, fax or email. Thereafter original cards will be collected approximately monthly for transcription to the eCRF. Participants will be contacted with regular reminders to complete the cards. As a further precaution against lost data, every participant will be individually contacted by telephone, email or in person to provide 24 hour dairy card data for 13^th^ May, 1st July and 31^st^ August 2013 to be used to assist in the statistical imputation of missing data in the event of incomplete data.

#### Secondary efficacy parameters

The Visual Analogue Scores will require completion every 2 weeks over the summer. Participants will be reminded to complete these as above and these will be collected at the same visits. Mini RQLQ and EQ-5D-5 L forms will be completed three times during the pollen season (June 12, June 26 and July 10) and once after the season on 4 September 2013. These forms will be collected at visits 8, 9 and 10.

### Safety

#### Specification, timing and recording of safety parameters

All adverse events and side effects will be recorded in the electronic case report form (eCRF) throughout the study regardless of their severity or relation to study participation.

Systemic allergic reactions to grass pollen intradermal injections are a theoretical possibility. As a precaution, all participants in this trial will be observed after the first intradermal injection for one hour, and if there is no systemic reaction, for 30 minutes after subsequent injections (since the dose of allergen given does not increase at later visits). All injections will be given in a clinical area with resuscitation facilities in the presence of a physician. If a participant has a Grade 2 reaction (see above) they may continue in the study but the observation period will be increased to 1 hour after each subsequent injection. In the event of a further Grade 2 reaction, that participant will not be permitted to continue in the study. In the event of a participant experiencing a Grade 1 reaction, the clinical observation period for that individual will also be maintained at 1 hour after subsequent injections. In the event of a single Grade 3 or 4 reaction, that participant will not be permitted to continue in the study.

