### Secondary endpoints in mechanistic assays

1) Inflammatory cells (eosinophils, mast cells, basophils, CD4+ T cells and Foxp3+ T cells) in skin biopsies collected 24 hours after receiving an intradermal diluent (negative control) and grass pollen allergen injection in September 2013.

2) Numbers of CRTH2^pos^CD203c^pos^CD3^neg^CD303^neg^ and CRTH2^pos^CD63^pos^CD3^neg^CD303^neg^ activated peripheral blood basophils cells following in vitro activation with grass pollen allergen (Visit 7).

3) Serum concentrations of *Phleum pratense*-specific IgG, IgG1, IgG4 and IgE at Visit 1 and Visit 7. These sera will also be tested for inhibitory activity against allergen-IgE complex binding to B cells.

4) Gene expression profiles of CD4+ T cells derived from skin biopsy explants in September 2013.

5) Cutaneous allergen-induced late response size measured in December 2013 (i.e. approx. 3 months after previous intradermal injection), March 2014 (6 months) or August 2014 (11–12 months).

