
### Trial medication

The active drug will be 10 Biological Units (BU) (33.3 SQ-U) of *Phleum pratense* soluble grass pollen extract (Aquagen SQ Timothy, ALK Abello, Reading UK) contained in a 20 microliter volume (i.e. 500 BU/ml (1666.7 SQ-U/ml)). Individual vials for each participant and each visit will be pre-prepared and pre-labeled by Guy’s Hospital Pharmacy under GMP conditions. In brief, Aquagen SQ Timothy Grass Pollen extract will be reconstituted in manufacturer-supplied diluent to the maximum recommended concentration (30'000 BU/ml (100'000 SQ-U/ml) i.e. 60-times final working strength; shelf life 6 months at 2-8°C after reconstitution) and 0.15 ml aliquoted into glass study vials. At each visit for intradermal injection the investigator will add 8.85 ml of clinical grade 0.9% normal saline at ambient temperature to the vial corresponding to that participant’s visit to achieve a 60-fold dilution. Twenty microliters will then be aspirated from this vial and administered directly. The allergen requires dilution on the day of administration as the recommended shelf life of Aquagen SQ Timothy Grass Pollen extract at 500 BU/ml (1666.7 SQ-U/ml) is only 14 days. Control drug will be histamine only, administered at a concentration of 100 mcg/ml. To help preserve blinding, histamine concentrations will be reduced to 30 mcg/ml for the 3^rd^ and 4^th^ injections, and 10 mcg/ml for 5, 6 and 7^th^ injections. To match the grass pollen extract dilution and preserve blinding, histamine will also be aliquoted into study vials at 60-times final working strength in 0.15 ml volumes, for further dilution with 8.85 ml of clinical grade 0.9% normal saline immediately prior to injection. Active and control study medications will appear identical.

Following manufacture, vials will be packed into individual dispensing packs that will be dispensed by pharmacy against a single study prescription for each study participant, covering all visits. At randomisation, an email will be sent from the randomisation system to the dispensing pharmacy. On receipt of a study prescription, the pharmacist will refer to this email to select an appropriate pack of active or control medication. The pack will then be fully blinded and dispensed. The blinded dispensed packs will thereafter be stored in the Clinical Research Facility in temperature monitored fridges in a secure environment.

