### Dosing regimen

A series of 7 intradermal active or control injections will be administered 2-weekly into the forearm between before the 2013 grass pollen season. The first injection will be administered between 18th February and 1st March 2013. We will aim to administer the 7th injection between 13th May and 24th May 2013. The injection site will again be alternated between left and right arms at each visit. Intradermal injections will be administered in a 20 microliter volume using a 29 gauge insulin syringe (Becton Dickinson Micro-FineTM). As a precaution against systemic allergic reactions all subjects will be observed for one hour after the first injection, and for 30 minutes after subsequent injections, in a clinical area with full resuscitation facilities.

Occasionally an injection may be administered too deeply (into subcutaneous tissue) resulting in failure to generate an immediate injection ‘bleb’ and subsequent characteristic wheal. For this reason, the injection site will be inspected in all subjects 15 minutes after each injection to confirm successful intradermal injection. In the absence of the typical wheal, the injection will be repeated at 1 cm from the original site.

In the event of acute illness (e.g. upper respiratory tract infection) or other unforeseeable circumstance, administration of active/control intervention may be postponed up to a maximum of 3 weeks since the previous injection, at the discretion of the investigator. The study team aim to perform over 90% of injections at 12–16 day intervals, although in exceptional circumstances the minimal interval permitted between injections may be reduced to 7 days. Onset of symptoms associated with the London grass pollen season generally falls between late May - early June. Therefore, if schedule adjustments result in a participant completing their 7 injections before 13th May 2013, the 7th injection will be repeated 12–16 days later in late May.

Following these injections, clinical outcomes will be measured during the summer of 2013. In September 2013 and either 3, 6 or 12 month later, all participants will also receive intradermal injections with diluent (negative control) or 10 BU (33.3 SQ-U) of grass pollen allergen. Although the trial will not be unblinded at this stage, these intradermal injections will be open label.

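### The reason given for cutting observation to 30 minutes, that the allergen dose never rises, is untrue for the control arm

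*Protocol article*

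**What the plan says.** Under Safety (Specification, timing and recording of safety parameters), the protocol names systemic allergic reaction to intradermal grass pollen as the hazard. As a precaution, "all participants in this trial will be observed after the first intradermal injection for one hour". If no systemic reaction occurs, observation is then shortened: "for 30 minutes after subsequent injections (since the dose of allergen given does not increase at later visits"). The Dosing regimen section gives the same timings without the reason: "all subjects will be observed for one hour after the first injection, and for 30 minutes after subsequent injections".

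Three other parts of the article determine who receives allergen and when:

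- Trial medication: active injections contain 10 BU (33.3 SQ-U) of extract. For the other arm, "Control drug will be histamine only".
- Dosing regimen: in September 2013, and again 3, 6 or 12 months later, "all participants will also receive intradermal injections with diluent (negative control) or 10 BU (33.3 SQ-U) of grass pollen allergen". It adds: "Although the trial will not be unblinded at this stage, these intradermal injections will be open label".
- Secondary efficacy parameters, on persistence of the skin response: "Each group will receive a follow-up intradermal injection of 10 BU (33.3 SQ-U) of grass pollen allergen". The mechanistic endpoints also describe skin biopsies taken "24 hours after receiving an intradermal diluent (negative control) and grass pollen allergen injection in September 2013".

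The article states no separate observation period for these post-season injections.

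**The concern.** The shorter observation rests on two ideas: the participant has already tolerated a first injection under an hour's observation, and no later injection carries more allergen. Neither applies to a control participant. The observed hour followed histamine, and the first intradermal allergen comes after the season, at an injection that the rule counts as a later one.

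Followed literally, the rule gives controls half the observation at their first 10 BU that the active arm gets at the identical first dose. The provision that restores the full hour after a Grade 1 or 2 reaction does not close the gap, because controls have had no study allergen to react to. Nor can staff fill it by judgement, since they remain blinded and cannot tell who is meeting allergen by this route for the first time.

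Participants may take an antihistamine after most injections but are asked not to at visits 10 and 11, when skin responses are measured. Visit 10 appears to be the September visit, because the quality-of-life forms dated 4 September are collected at visits 8, 9 and 10. On that reading, some or all controls would have their first intradermal allergen without antihistamine cover as well as with the shorter observation.

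**Working it through.** **The dose.** From Trial medication: 0.15 ml of stock at 30,000 BU/ml (100,000 SQ-U/ml), 8.85 ml of saline added, 20 microlitres injected.

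- Dilution factor: (0.15 + 8.85) / 0.15 = 9.00 / 0.15 = 60.
- In BU: 30,000 / 60 = 500 BU/ml, and 500 × 0.02 ml = 10 BU.
- In SQ-U: 100,000 / 60 = 1,666.7 SQ-U/ml, and 1,666.7 × 0.02 ml = 33.3 SQ-U.

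Both agree with the stated dose.

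**Intradermal allergen by arm and phase.**

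| Phase | Active | Control |
|---|---|---|
| Treatment injections 1 to 7 or 8 | 10 BU each | 0 BU (histamine) |
| First open-label allergen injection, post-season | 10 BU | 10 BU |
| Change at that injection | 10 to 10 BU: none | 0 to 10 BU |

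The Dosing regimen wording, diluent or allergen, leaves it slightly unclear whether every control has allergen in September 2013. This affects only which visit comes first: every follow-up group receives 10 BU at 3, 6 or 12 months. On either reading, a control who stays in the trial has a first intradermal allergen dose post-season and open label.

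**How many.** With 1:1 randomisation:

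- 90 randomised: 90 / 2 = 45 controls; after 10% dropout, 45 × 0.9 = 40.5, about 40.
- 100 randomised (the stated maximum): 100 / 2 = 50 controls; after 10% dropout, 50 × 0.9 = 45.

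The stated reason is therefore untrue for 45 of 90 planned participants, or half. Applying the 10% allowance to attendance at the open-label visits is an assumption; the protocol sets it for the primary outcome.

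**What cannot be computed.** The article gives neither the frequency nor the timing of systemic reactions, so the number expected between 30 and 60 minutes cannot be estimated.

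**The case against.** The strongest reply concerns scope. In the Dosing regimen section the same timings sit in the paragraph on the pre-season series, and the September and follow-up injections are introduced later as a separate phase with a different purpose. Within the treatment course nobody's allergen dose rises: it is constant in one arm and absent in the other. If the safety section merely restates that rule, its reason is true. One could even read the first injection there as the first grass pollen injection, which would give controls their hour, though that is the less natural reading.

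The treatment-course reading is fair for Dosing regimen. It does not fit the safety section, which addresses all participants in the trial and speaks of later visits without limit. If the rule did stop at the treatment course, the article would give no observation time for the open-label allergen injections, and the wording would still need a stated scope.

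A second reply is that this is a condensed article, and visit-level procedures for the open-label phase may be in the full protocol. That is possible, and it would reduce the correction to the reason and its scope. The point, however, is a stated reason that does not hold for half the trial, rather than a missing detail.

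A third reply is that the risk is small. This stands. The dose is about 7 ng of Phl p 5, a physician and resuscitation facilities are present at all injections, all participants have had a grass pollen skin prick test, and a history of life-threatening anaphylaxis is an exclusion. Nothing in the document shows that 30 minutes is inadequate. But the protocol itself judged a first 10 BU dose to merit an hour in the active arm, and consistency asks the same for controls.

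**Conclusion.** The concern holds. As written, the safety rule covers the whole trial, and its reason is wrong for the control arm: 45 of 90 planned participants, about 40 of whom would reach the injection in question if 10% drop out. For them intradermal allergen rises from 0 to 10 BU with 30 minutes of observation rather than 60.

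The conclusion rests on reading the safety section's unrestricted wording at face value and on no other rule for the open-label visits in the full protocol, which was not available. It is a modest safety correction that should be made. It does not bear on sample size, type I error or the primary analysis, and no claim is made about how many reactions the longer observation would catch.

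**What to change.** Amend the observation rule in both Safety and Dosing regimen:

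- Observe every participant for one hour after the first open-label allergen injection, whichever visit that is. If no systemic reaction occurs, 30 minutes suffices for later ones.
- Apply this to both arms. Allocation is still blinded, and a rule for controls alone would reveal it.
- Limit the constant-dose reason to the 7 or 8 treatment injections.

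If the full protocol already sets an hour for the open-label visits, only the last change is needed.

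The cost is a short amendment and about half an hour at one existing visit per participant: 0.5 × 90 = 45 participant-hours, or 0.5 × 81 = 40.5 after 10% dropout, or 0.5 × 100 = 50 if 100 are randomised and all attend. No endpoint, analysis or sample size changes.

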#### Treatment stopping rules

The trial will be stopped in the event of five grade 3 reactions or a single grade 4 reaction. In addition the trial may be prematurely discontinued by the Sponsor, Chief Investigator or Regulatory Authority on the basis of new safety information or for other reasons given by the Data Monitoring & Ethics Committee/Trial Steering Committee regulatory authority or ethics committee. The trial may also be prematurely discontinued due to lack of recruitment or upon advice from a Trial Steering Committee who will advise on whether to continue or discontinue the study and make a recommendation to the sponsor. If the study is prematurely discontinued, participants will be informed and no further participant data will be collected.

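### For the same systemic reactions one section stops study therapy and keeps follow-up while another ends study participation, and a trial-level stop ends all data collection

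*Protocol article*

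**What the plan says.** Three parts of the protocol article deal with what follows a systemic reaction.

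- **Withdrawal of participants.** The list opens with "The study therapy (active or control) will be discontinued for any of the following reasons", and its third item is "Two Grade 2 systemic reactions, or a single systemic reaction of Grade 3 or above after administration of study therapy". The section then separates leaving the drug from leaving the trial: "Should a participant withdraw from study drug only, efforts will be made to continue to obtain follow-up data, with the permission of the patient".
- **Specification, timing and recording of safety parameters.** After one Grade 2 reaction participants are told that "they may continue in the study but the observation period will be increased to 1 hour after each subsequent injection". For a second: "In the event of a further Grade 2 reaction, that participant will not be permitted to continue in the study". For the higher grades: "In the event of a single Grade 3 or 4 reaction, that participant will not be permitted to continue in the study".
- **Treatment stopping rules.** The whole trial stops at five Grade 3 reactions or one Grade 4 reaction, and may also stop for recruitment, new safety information or other reasons. In any such event: "If the study is prematurely discontinued, participants will be informed and no further participant data will be collected".

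Statistical analysis compares the arms on randomised patients with a Van Elteren test. It plans multiple imputation if the assumed 10% non-evaluable rate is observed, and a sensitivity analysis for departures from missing at random.

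**The concern.** The triggers in the first two sections are identical but the consequences are not. One stops the injections and tries to keep the participant's data; the other, taken at its word, ends participation. Site staff cannot apply both.

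The timing makes this matter. Injections run from 18 February to about 24 May 2013, and the primary diary window opens on 13 May. Someone who leaves the study during the injection course supplies little or no primary outcome. The duty to record adverse events is also framed as lasting throughout the study, so a literal exit would end it for the people with the most serious reactions. If reacting is related to treatment or to later hay fever severity, the gaps are informative.

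The trial-level rule is a separate problem. It is explicit, it applies to both arms, and it makes no exception for diaries or safety follow-up of people already injected.

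**Working it through.** **1. Rules side by side**

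| Trigger | Withdrawal of participants | Safety section |
|---|---|---|
| Second Grade 2 | Study therapy stopped; follow-up sought from those off drug | May not continue in the study |
| One Grade 3 or 4 | Study therapy stopped; follow-up sought from those off drug | May not continue in the study |

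Only Treatment stopping rules says in terms that data collection ends, and there it ends for everyone.

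**2. Timing.** The window from 13 May to 31 August is 19 + 30 + 31 + 31 = 111 days. The seventh injection is aimed at 13 to 24 May. A trial-level stop in that period would leave at most 12 of 111 diary days (11%). An earlier stop would leave none.

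**3. The plan's own sample size.** 35 × 1.15 = 40.25, taken as 40; 40/0.9 = 44.4, rounded up to 45 per arm, total 90. This reproduces. The starting figure of 35 per arm cannot be checked because no effect or SD is given. The standardised effect it implies (normal approximation, 90% power, two-sided 0.05) is d = (1.960 + 1.282)/√(35/2) = 0.775.

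**4. How many people.** The fifth Grade 3 reaction stops the trial, so at most four single-Grade-3 reactors can occur in a trial that continues: 4/90 = 4.4% overall, or 4/45 = 8.9% of the active arm if all four are active. Removals after a second Grade 2 reaction have no such cap. The article gives no expected reaction rate, so the number lost (k) is an assumption.

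**5. Power and bias if k active participants are lost**

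- Power = Φ(d√ARE / √(1/(40−k) + 1/40) − 1.960), with the k losses on top of the planned 10%. ARE is the asymptotic relative efficiency of the rank test, set to its lower bound 0.864 or to 1.
- Bias from omitting them = (k/45) × s, where s is how much worse they score than other active participants, assumed 0.25 to 1.0 SD.

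| k | Power, ARE 0.864 | Power, ARE 1 | Bias (SD) | Bias as % of d |
|---|---|---|---|---|
| 0 | 0.896 | 0.934 | 0 | 0 |
| 2 | 0.889 | 0.928 | 0.011 to 0.044 | 1.4 to 5.7 |
| 4 | 0.880 | 0.921 | 0.022 to 0.089 | 2.9 to 11.5 |
| 9 | 0.853 | 0.899 | 0.050 to 0.200 | 6.5 to 25.8 |

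For k = 4 at ARE 0.864: 0.775 × √0.864 / √(1/36 + 1/40) − 1.960 = 1.175, so power is 0.880, a loss of 0.016. The bias limits are (4/45) × 0.25 = 0.022 and (4/45) × 1.0 = 0.089.

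**6. Imputation condition.** Multiple imputation is tied to the 10% rate, which is 9 of 90. Four reactors alone (4.4%) would not reach it, so the text leaves unclear whether their missing scores would be imputed. Other drop-out could bring the total to that rate.

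**The case against.** The strongest reply is that the Safety section is only loosely worded. It never mentions data collection, and its sentence on a first Grade 2 reaction links continuing in the study to later injections. Read with Withdrawal of participants, it may mean no more than an end to injections. It may also have been meant to cover the open-label allergen injections in September and at 3, 6 or 12 months. This is a fair reading and may be the intended one, but the text does not say so, and the literal reading loses data.

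A reader might infer that reactors are excluded from the primary analysis, or that analysing everyone randomised becomes impossible. The documents do not support that: no section excludes them, the analysis is of randomised patients, and imputation and a sensitivity analysis are planned. Every participant is also to be contacted individually for diary data on 13 May, 1 July and 31 August to help imputation. These safeguards stand, but they are weaker than collected diaries, and the individual contacts would lapse for anyone literally out of the study.

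A reader might also infer that the losses fall only on the active arm. The Safety section links systemic reactions to grass pollen injections and controls receive histamine, so this is plausible. But the section calls such reactions a theoretical possibility and gives no rate for either arm. The trial-level rule does not select reactors at all.

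Finally, the detailed adverse-event procedures are in Additional file 3, which is not shown and may provide for safety follow-up after a stop.

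**Conclusion.** The concern holds as a conflict between stated rules. For identical triggers the article both stops therapy with follow-up sought and bars the participant from continuing in the study. Read literally, the second rule makes reactors' primary outcome and later safety data avoidably and probably informatively missing, and the analysis plan only partly repairs that. Separately, the trial-level rule would forfeit most diary data in both arms if it took effect around the last injections and, as worded, safety follow-up of people already injected.

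The numerical effect of the individual rule is modest. With four reactors, power falls by about 1.6 points, and bias is 2.9% to 11.5% of the implied effect. Those figures assume that all four are active, give no diary data, score 0.25 to 1.0 SD worse and are left out without imputation. They are on a mean-difference scale, whereas the planned test is rank-based, so they show order of magnitude only. The reason to act is informative missingness that costs little to avoid.

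**What to change.** Reconcile Withdrawal of participants, the Safety section and Treatment stopping rules so that decisions about treatment are separate from decisions about data collection:

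- State that diary, questionnaire and adverse-event follow-up continues, with consent, for participants who stop injections and after a trial-level stop.
- State that these participants are analysed in the arm to which they were randomised.
- Ask the sponsor to clarify what continuing in the study covers in the Safety section, including whether it extends to the later open-label injections.
- Make clear whether imputation applies when less than 10% of data are missing.

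The reaction triggers and their consequences for treatment are for the sponsor to settle and are not judged here. The cost is a wording amendment. The sample size stays at 90, and the diaries, reminders and individual contacts are already planned for every participant.
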